#### Register-based information

Information on vital status, use of mental health services, both as in- and outpatient, number of days of admission, sickness absence and use of social benefits will be gathered from the DREAM database or the Danish Psychiatric Case Register (DPCR) [53]. DPCR is the patient-registry system used by the mental health services in Denmark; it contains information on all hospital admissions, number and duration, outpatient contacts and deaths.

An overview of all data collected and the source of collection is shown in Table 1.

**Table 1 T1:** Data collection at baseline and follow-up

**Source of collection**	**Assessment**	**Baseline**	**12 months follow-up**	**24 months follow-up**
Interview	Hamilton Depression Scale (HAM-D6)	x	x	x
	Hamilton Anxiety Scale (HAM-A6)	x	x	x
	Bech-Rafaelsen Mania Scale (MAS)	x	x	x
	Personal and Social Perfomance scale (PSP)	x	x	x
	Global Assessment of Functioning (GAF)	x	x	x
	Suicidal ideation	x	x	x
Self report	Sheehan Disability Scale (SDS)	x	x	x
	Quality of life (WHO-5)	x	x	x
	Empowerment Scale	x	x	x
	Changes Questionnaire	x	x	x
	Client Satisfaction Questionnaire (CSQ)	x	x	x
	Health-related quality of life EQ-5D (EuroQol)	x	x	x
Hospital records	Number of hospital admissions		x	x
	Length of hospital admissions		x	x
	Use of outpatient services		x	x
	Death (all causes)		x	x
	Suicide		x	x
Dream/interview	Sociodemographic information	x	x	x
Dream	Labour market affiliation	x	x	x
Dream/interview	Civil status	x	x	x
DPCR	First contact with mental health care	x		
Dream/interview	Children	x	x	x
Dream/interview	Education	x	x	x
Dream/interview	Cohabitation status	x	x	x
DPCR	Use of mental health service		x	x
Dream	Number of sick days		x	x
Dream	Use of social benefits		x	x
Self report	Treatment and use of other service from the social and healthcare sector		x	
Self report	Service provided by Sherpa		x	

DPCR, The Danish Psychiatric Case Register.

All data will be handled in accordance with the Danish Data Protection Agency.

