### Inclusion criteria

Participants must be aged 18 to 60 years, diagnosed by the referring psychiatrists according to the International Classification of Diseases 10th edition criteria of affective disorders (F30-39) or anxiety disorders (F40-41), and not have had contact with mental health services for more than 3 years. They must have been employed or enrolled in education at some time during the past 2 years. They must have a pronounced wish to return to either employment or education, but not being ready to do so within the following 3 months, and equal to ‘match group’ 2 or 3. (‘Match groups’ are categories used by the job centres in Denmark [33] to estimate how far people are from the labour market. Match group 2 refers to people who can participate in pre-vocational training or courses, but who would not be able to take an ordinary job and be off social benefits within 3 months. Match group 3 refers to people with problems so severe that they cannot work or participate in pre-vocational training). Participants must have the ability to read and understand Danish, and give informed consent verbally and in writing.

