### Statistical analyses

Data analyses will be based on the intention-to-treat principle, which means that data will be included in the group to which the participant was randomised, regardless of intervention received. Data will be analysed using the IBM SPSS Statistics version 20 for Windows.

To assess homogeneity of the two groups at baseline, demographic data such as age, gender, marital status, education level, support (social benefits, social security and so forth), diagnosis and Match group at baseline will be presented.

Dichotomous outcomes will be analysed using logistic regression. For primary and secondary outcomes, an unadjusted analysis of the effect of the Sherpa method as an add-on to treatment-as-usual versus exclusively treatment-as-usual will be carried out, as well as an analysis adjusted for stratification variables (diagnosis and Match group). Multiple multivariate imputations will be used to impute a distribution of missing values.

Continuous outcomes will be analysed in a mixed model with repeated measurements. This model is based on the assumption that data are missing at random or missing completely at random [60].

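### The adjusted analysis of days in employment or education uses no pre-randomisation count, and Table 1 gives several register counts no look-back: a cheap gain in precision is left unused

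*Protocol article*

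**What the plan says.** All references are to the protocol article.

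- **Register-based information.** The text states that "sickness absence and use of social benefits will be gathered from the DREAM database or the Danish Psychiatric Case Register (DPCR"), without a time window.
- **Table 1**, introduced as an overview of all the data collected. The DREAM rows "Number of sick days" and "use of social benefits", the DPCR row "Use of mental health service", and the rows for number and length of admissions (the first being "Number of hospital admissions") are crossed at 12 and 24 months and blank at baseline. Table 1 labels the admission rows as hospital records, although the text above it names DREAM or DPCR.
- **Also in Table 1.** The DREAM row "Labour market affiliation" is crossed at baseline, 12 and 24 months. First contact with mental health care is taken from DPCR at baseline only.
- **Outcomes.** Days in competitive employment or education is secondary outcome 1, assessed at 12 and 24 months. Employment and education information comes from DREAM.
- **Statistical analyses.** Primary and secondary outcomes get an unadjusted analysis, "as well as an analysis adjusted for stratification variables (diagnosis and Match group"). Continuous outcomes go into a repeated-measures mixed model. No prior count is named as a covariate.
- **Inclusion criteria.** "They must have been employed or enrolled in education at some time during the past 2 years".

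**The concern.** A person's days in work before randomisation plausibly predict days in work afterwards. The entry rule lets that history vary widely: one participant may have worked until last month, another may have stopped nearly 2 years ago. Two Match groups and four diagnostic strata are unlikely to capture all of that spread.

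The interview and self-report scales in Table 1 all have a baseline value. Several of the register counts do not, although history is easiest to obtain from a register. What is at stake is the width of the interval for secondary outcome 1. For the other counts it is also whether readers can see that the arms were alike in earlier sickness absence and service use.

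**Working it through.** **1. What is already read for the period up to baseline**

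| Item | Source in Table 1 | Baseline | 12 and 24 months |
|---|---|---|---|
| Labour market affiliation | DREAM | yes | yes |
| First contact with mental health care | DPCR | yes | no |
| Sick days; benefit use | DREAM | no | yes |
| Mental health service use | DPCR | no | yes |
| Number and length of admissions | Hospital records | no | yes |

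Both registers are therefore consulted for baseline or earlier. The article describes DPCR as holding all admissions with their number and duration, and DREAM as holding employment, sickness leave and benefits. A look-back needs no new source for the DREAM and DPCR rows.

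**2. Inputs for secondary outcome 1**

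- From Table 2: difference 60 days at 12 months, SD 150 days, type I error 5% (taken as two-sided; the article does not say), stated power 95%.
- From Power and sample size: 162 per arm.
- Assumed: correlation r between prior days and outcome days, shown at 0.3 and 0.5. SD 150 is treated as the residual SD before the prior count is added, so r means correlation beyond what diagnosis and Match group explain.

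**3. Reproducing the stated power without a prior count**

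- SE = 150 × √(2/162) = 150 × 0.1111 = 16.67 days.
- 95% CI half-width = 1.96 × 16.67 = 32.7 days.
- Power = Φ(60/16.67 − 1.96) = Φ(1.64) = 94.9%. The noncentral t gives 94.8%. The stated 95% is reproduced.

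**4. Adding a prior-days covariate**

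Residual SD = 150 × √(1 − r²), with the rest as in step 3.

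| r (assumed) | Variance removed (r²) | Residual SD | SE | CI half-width | Power, 60 days | Power, 45 days |
|---|---|---|---|---|---|---|
| 0 | 0% | 150.0 | 16.67 | 32.7 | 94.9% | 77.0% |
| 0.3 | 9% | 143.1 | 15.90 | 31.2 | 96.5% | 80.8% |
| 0.5 | 25% | 129.9 | 14.43 | 28.3 | 98.6% | 87.7% |

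The 45-day column is an illustration and not a figure from the protocol. It shows that the gain matters more if the true difference is smaller than planned.

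**5. Chance imbalance**

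The SE of the difference between arms in any baseline count is √(2/162) = 0.11 SD, so the 95% range is about ±0.22 SD.

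**6. The other counts**

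The article gives no SD, effect size or power for sick days, benefit use, service use or admissions. Only the variance fraction r² can be stated: 9% at r = 0.3 and 25% at r = 0.5.

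**The case against.** The case against is substantial. Adjusting for the stratification variables alone is a valid method, nothing is misstated, and an analysis plan that is not shown may add covariates. Secondary outcome 1 already has 95% power as planned. The other counts are exploratory or have no stated rank. Entry rules narrow the range of work history, and Match group may already carry part of it, so r could be low. Register history can be extracted later, so a blank cell loses nothing for good.

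Most of this stands, and it limits the point to an optional improvement. It does not remove the point. The article itself names the adjusted model and presents Table 1 as complete. A covariate and its window are also best fixed before results are seen.

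A reader might infer more than the documents support:

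- *That no prior employment information is collected.* The baseline cross for labour market affiliation contradicts this; only its form (status or day count) is unstated.
- *That benefits are undocumented at baseline.* Type of support will be presented, though as a type and not a count.
- *That all the counts come from registers.* Table 1 labels admissions as hospital records.
- *That the comparison is biased.* Randomisation prevents that.
- *That the gain equals 32 to 108 extra participants* (324/0.91 = 356; 324/0.75 = 432). The 324 was set by the binary primary outcome, so the conversion does not describe a day count.

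**Conclusion.** The point holds as a minor, low-cost improvement. The stated adjusted analysis of secondary outcome 1 leaves out prior days in employment or education, although the source is already read at baseline and eligibility allows that history to vary. Several other counts have no scheduled look-back.

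The benefit is precision only: about 1.5 days off the CI half-width at r = 0.3 (32.7 − 31.2) and 4.4 days at r = 0.5 (32.7 − 28.3). Power for the planned difference rises by 1.6 or 3.7 percentage points from a base that is already sufficient. These figures rest on an assumed r and on the 12-month SD in Table 2; no 24-month SD is given. For the remaining counts the gain cannot be expressed in their own units.

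**What to change.** 1. State whether the baseline DREAM reading of labour market affiliation is a status or a history of days.
2. Extract days in employment or education from DREAM for a fixed window before randomisation, for example the 24 months that the eligibility rule already covers.
3. Name that count as a prespecified covariate in the adjusted model for secondary outcome 1, beside diagnosis and Match group. Keep the unadjusted analysis as planned.
4. Apply the same look-back to the DREAM and DPCR counts (sick days, benefit use, mental health service use, and admissions as held in DPCR). Add the baseline crosses in Table 1, and use these counts for baseline description and for any exploratory adjusted analyses.
5. Settle whether admissions come from hospital records or DPCR, since the text and Table 1 differ.

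The cost is a longer date range in extractions that are already planned and one more covariate per model. No participant contact is needed.

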### Power and sample size

We have been unable to find data on how many people actually return to employment or education with traditional pre-vocational training after anxiety or an affective disorder in either the Danish or the national literature. Therefore, we have leaned towards the findings in OPUS, a programme in which young people with schizophrenia receive early intensive treatment for 24 months. In OPUS it was found that 40% returned to employment or education versus 32% in the control group ([name], personal communication). Based on this knowledge, we conservatively estimate that 30% will regain employment or education following traditional pre-vocational training.

Across a broad range of studies of severe mental illness and IPS versus traditional pre-vocational training, studies show that approximately 50% more of the participants in the IPS groups regain employment compared to the control groups [15]. We therefore expect to find that 50% more of the participants in the Sherpa group compared to the control group will regain employment or education, and have estimated the true difference in the experimental and control group to be 15%-points; hence, 45% of the participants in the Sherpa group will regain employment. To be able to reject the null hypothesis that the proportion of participants who regain employment or education in the experimental and control group is equal with a probability (power) of 80%, 162 participants will be required in each group (total 324). The Type I error probability associated with the test of this null hypothesis is 5%. We also estimated the sample size using a power of 90%. This resulted in a total of 434 participants (2 × 217). We therefore plan to recruit a minimum of 324 participants and, in order to reduce the risk of type II error, we will aim to recruit up to 434 participants, if possible, in the 2-year recruitment period. Power and sample size calculations have been made using the PS Power and Sample Size Calculations program version 3.0.14 [55,56].

The power for the secondary outcomes has been estimated based on a number of 162 participants in each group (Table 2). Since it has not been possible to find studies or trials similar to our trial regarding patient group or method, expected effect size concerning number of days in employment or education has been conservatively estimated. The studies found [1,9,19,21,22,57-59] did not find any difference between groups after 12 months considering GAF-F, WHO-5, HAM-D6 or HAM-A6. If we find a difference between groups, we want it to be clinically relevant; therefore, the effect sizes equals the clinically relevant difference.

**Table 2 T2:** Power calculations for secondary outcomes, calculated from a sample size of 324 participants

**Measure**	**Mean difference**	**Standard deviation of the pooled mean**	**Type I error**	**Reference**	**Power**
No of days of competitive employment of education at 12 months	60 days	150 days	5%	Kin W 2008 [21], Burns 2007 [14]	95%
GAF-F	5	15	5%	Hoffmann 2011 [19], Howard 2010 [58]	85%
WHO-5	10	19	5%	Latimer 2006 [22], Burns 2009 [14]	99%
HAM-D6	2	4	5%	Wang 2007 [10], Lexis 2011 [9], Brouwers 2006 [1], Van Oostrom 2010 [59]	99%
HAM-A6	2	4	5%	Wang 2007 [10], Lexis 2011 [9], Brouwers 2006 [1], Van Oostrom 2010 [59]	99%

GAF, Global Assessment of Functioning; HAM-A6, Hamilton Anxiety Scale; HAM-D6, Hamilton Depression Scale; WHO-5, WHO-Five Well-being Index.

### Statistical analyses

Data analyses will be based on the intention-to-treat principle, which means that data will be included in the group to which the participant was randomised, regardless of intervention received. Data will be analysed using the IBM SPSS Statistics version 20 for Windows.

To assess homogeneity of the two groups at baseline, demographic data such as age, gender, marital status, education level, support (social benefits, social security and so forth), diagnosis and Match group at baseline will be presented.

Dichotomous outcomes will be analysed using logistic regression. For primary and secondary outcomes, an unadjusted analysis of the effect of the Sherpa method as an add-on to treatment-as-usual versus exclusively treatment-as-usual will be carried out, as well as an analysis adjusted for stratification variables (diagnosis and Match group). Multiple multivariate imputations will be used to impute a distribution of missing values.

Continuous outcomes will be analysed in a mixed model with repeated measurements. This model is based on the assumption that data are missing at random or missing completely at random [60].

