### Assessments

Participants will be interviewed and asked to fill in questionnaires at baseline and at follow-up after 12 and 24 months. At baseline, socio-demographic information on education, income base, marital status, number of children and somatic disease will be collected.

To confirm the diagnosis, the Mini International Neuropsychiatric Interview (MINI) [37] is used at baseline. Baseline interviews will always be face-to-face, most often in the participants’ home. Participants will fill in questionnaires at home.

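### The stated adjustment set leaves out the baseline HAM-D6, HAM-A6, GAF-F and WHO-5 scores, and nothing in the mixed-model wording secures their efficient use

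*Protocol article*

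**What the plan says.** The Statistical analyses section of the Protocol article plans, for primary and secondary outcomes, an unadjusted comparison "as well as an analysis adjusted for stratification variables (diagnosis and Match group"). It then says "Continuous outcomes will be analysed in a mixed model with repeated measurements", under a missing-at-random or missing-completely-at-random assumption. It does not say whether the baseline value is one of those repeated measurements, whether baseline means are constrained, or which contrast gives the treatment effect.

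The Assessments section states: "Participants will be interviewed and asked to fill in questionnaires at baseline and at follow-up after 12 and 24 months". Table 1 marks each scale at all three times:

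- "Hamilton Depression Scale (HAM-D6) x x x"
- "Hamilton Anxiety Scale (HAM-A6) x x x"
- "Global Assessment of Functioning (GAF) x x x"
- "Quality of life (WHO-5) x x x"

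Four of the five secondary outcomes therefore have their own baseline value on file. None of these values is in the named adjustment set. Table 2 gives power at 162 per arm as 85% for GAF-F and 99% for each of WHO-5, HAM-D6 and HAM-A6.

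**The concern.** The baseline score of a symptom or functioning scale is usually among the best predictors of its later value. Using it costs nothing once it is collected, and it reduces the variance of the treatment effect whenever the baseline to follow-up correlation differs from zero. The article states an adjustment set and this score is not in it.

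A repeated-measures model does not by itself make up for that. Its precision depends on whether baseline is in the model and on what is assumed about the baseline means. At stake are wider confidence intervals than necessary for the four scales and, for GAF-F, some power. In addition, three plausible contrasts (follow-up only, change from baseline, baseline-adjusted) can give different estimates from the same data, and the article does not say which will be reported.

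**Working it through.** **Inputs from the Protocol article.** 162 per arm (Power and sample size); difference and SD from Table 2: GAF-F 5 and 15, WHO-5 10 and 19, HAM-D6 and HAM-A6 2 and 4; type I error 5%, taken as two-sided. I take the GAF entry in Table 1 to include the functioning score that Table 2 calls GAF-F.

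**Assumed.** The correlation r between the baseline and follow-up score is not in the document; I use 0.3, 0.5 and 0.6. SDs are taken as equal at baseline and follow-up, and data as complete.

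**Step 1: reproduce Table 2.** SE = SD × √(2/n), and power ≈ Φ(difference/SE − 1.96).

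- GAF-F: SE = 15 × √(2/162) = 1.667; 5/1.667 = 3.00; power 85.1% (84.9% by noncentral t). Stated: 85%.
- WHO-5: SE 2.111, power 99.7%. Stated: 99%.
- HAM-D6 and HAM-A6: SE 0.444, power 99.5%. Stated: 99%.

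Table 2 is thus a two-sided, unadjusted two-sample calculation with the raw SD. A one-sided test would give 91.2% for GAF-F, which does not fit.

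**Step 2: variance of the treatment contrast under each reading of the model**, relative to a comparison of follow-up values alone.

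| Handling of baseline | Factor | r = 0.3 | r = 0.5 | r = 0.6 |
|---|---|---|---|---|
| Left out, or in the response unconstrained with the follow-up contrast reported | 1 | 1.00 | 1.00 | 1.00 |
| In the response unconstrained, change contrast reported | 2(1−r) | 1.40 | 1.00 | 0.80 |
| Covariate, or in the response with equal baseline means | 1−r² | 0.91 | 0.75 | 0.64 |

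Since 2(1−r) − (1−r²) = (1−r)², the change contrast is less precise than the adjusted one for every r below 1. It beats follow-up only just when r exceeds 0.5.

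A simulation with complete data (r = 0.5, SD 15, 162 per arm) gave empirical SEs of 1.66 for follow-up only, 1.66 for change and 1.43 for the baseline-adjusted estimate. The formulas give 1.667, 1.667 and 1.667 × √0.75 = 1.443.

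**Step 3: gain if baseline would otherwise be left out.** The variance reduction is r²: 9%, 25% and 36%. For GAF-F:

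| r | SE | Power | Equivalent n per arm, 162/(1−r²) |
|---|---|---|---|
| not used | 1.667 | 85.1% | 162 |
| 0.3 | 1.590 | 88.2% | 178 |
| 0.5 | 1.443 | 93.4% | 216 |
| 0.6 | 1.333 | 96.3% | 253 |

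At r = 0.5 the confidence interval is 13% narrower (1 − √0.75). For HAM-D6 and HAM-A6 the SE goes from 0.444 to 0.424, 0.385 and 0.356. For WHO-5 it goes from 2.111 to 2.014, 1.828 and 1.689. Power for these three was above 99% already.

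**Step 4: gain if an unconstrained change contrast would otherwise be reported.** The variance falls from 1.40 to 0.91, 1.00 to 0.75 and 0.80 to 0.64, which is 35%, 25% and 20%. GAF-F power for the change contrast is 72% at r = 0.3 (SE 1.667 × √1.40 = 1.972; Φ(2.535 − 1.96)), 85% at r = 0.5, and 92% at r = 0.6 (SE 1.667 × √0.80 = 1.491; Φ(3.354 − 1.96)).

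**Step 5: gain if a constrained baseline model is already intended.** None. With complete data it uses the same estimator as covariate adjustment.

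**The case against.** The strongest reply is that a variable can inform a mixed model without being listed as a covariate. The scales are measured at baseline, 12 and 24 months, so the repeated measurements may well include baseline, and how it enters is a detail that an article commonly leaves to the full protocol or SAP. That stands in part. A reader might infer from the covariate list that the baseline information is definitely discarded, but the text does not support this: a constrained baseline model is not ruled out, and under it nothing is lost. What remains is that the article does state an adjustment set for the secondary outcomes, that this set omits the baseline scores, and that two of the three ways to complete the model lose precision.

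It can also be said that the consequence is small. That stands. Three of the four scales have power to spare, GAF-F at 85% is above the 80% chosen for the primary outcome, and the binary register-based primary outcome and the total of 324 are not involved.

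Two further inferences would go too far. Table 2 is not in error: it reproduces from its own inputs, matches the planned unadjusted analysis, and is conservative if baseline is then used as a covariate. Nor does omitting baseline bias the effect estimate: under central stratified randomisation the unadjusted estimate is unbiased, and chance imbalance in baseline scores is the same precision issue seen in a single realised sample.

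**Conclusion.** The point holds as a minor one about four secondary outcomes, with moderate confidence. The article names only diagnosis and Match group for adjustment and does not secure the efficient use of baseline scores that it collects. The loss ranges from zero (constrained baseline model) upward. If baseline is left out, adjustment would remove 9%, 25% or 36% of the variance at r = 0.3, 0.5 or 0.6 and lift GAF-F power from 85% to about 88%, 93% or 96%. If an unconstrained change contrast is used, the reduction is 35%, 25% or 20%. WHO-5, HAM-D6 and HAM-A6 gain narrower intervals and almost no power. These sizes rest on assumed correlations, equal SDs over time and complete data. That some precision is gained over leaving baseline out needs only that r is not zero.

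**What to change.** Add a sentence to Statistical analyses: for each of HAM-D6, HAM-A6, GAF-F and WHO-5, the mixed model takes the 12- and 24-month values as outcomes, with the baseline score (its effect allowed to differ by time point), diagnosis stratum and Match group as covariates, and the treatment effect is reported at 12 and at 24 months. Equivalently, specify a constrained longitudinal model with baseline in the response and equal baseline means across arms, adjusted for the same stratification variables. The planned unadjusted analysis can be kept beside it. Table 2 can stay, labelled as a conservative unadjusted calculation.

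The cost is one line of analysis wording, with no new data, no further visits and no change to the sample size.

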### Participant withdrawal

Participants can choose to withdraw from the trial at any time during the intervention period, without it having any consequences for the treatment they will receive, but they will politely be reminded of the importance of their participation. Participants who choose to withdraw from the trial are asked to specify which aspects of the trial they withdraw from: participation in the experimental intervention, participation in the follow-up interviews, use of data collected at central registers, or complete withdrawal including use of already collected data.

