## Discussion

The IPS-MA method is based on a 1-year pilot study and the evidence supporting IPS in other countries. To our knowledge this is the first trial investigating the effect of a supported employment intervention when provided to people with a recently diagnosed affective disorder or anxiety disorder, an area with only sparse knowledge about effective interventions. A strength of the study is the centralised computer-based randomisation which ensures an adequate generation of the allocation sequence and adequate allocation concealment. The use of blinded outcome assessors for the primary outcome and the fact that it is a register-based outcome as well as the use of intention-to-treat analysis decreases the risk of biased effect estimates. The trial is registered at http://www.clinicaltrials.gov, which helps preventing selective and incomplete outcome reporting. The primary outcome is register-based, which ensures almost complete follow-up due to the comprehensiveness of Danish registers.

The fact that we monitor fidelity to the IPS-MA method on a yearly basis is another strength of this trial. We do so to ensure that mentors and career counsellors are true to the method.

A limitation to this trial is that we are not able to blind participants, mentors or carers. Some might argue that it is difficult to sustain the blinding of the assessor during follow-up, and this is certainly a risk of bias. Should blinding be violated, a second assessor will complete the follow-up interview.

Even though participants are recruited from mental health centres throughout the Capital Region of Denmark, and should be fairly representative of the population in the region, we may have a reduced external validity. As it is the staff at the mental health centres that identify eligible participants, not everybody with an affective disorder or anxiety disorder eligible might have been asked to participate; patients are not systematically screened for eligibility.

Due to differences in labour markets and well-fare systems, results may not be directly generalisable to other countries.

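### It is unclear whether multiple imputation covers HAM-D6, HAM-A6, GAF and WHO-5, and register data on work, sick days and service use should be auxiliary variables for their missing values.

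*Protocol article*

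**What the plan says.** All of this is in the protocol article.

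- **Model.** Under Statistical analyses: "Continuous outcomes will be analysed in a mixed model with repeated measurements". The stated assumption is: "This model is based on the assumption that data are missing at random or missing completely at random".
- **Adjustment.** For primary and secondary outcomes an unadjusted analysis is planned, "as well as an analysis adjusted for stratification variables (diagnosis and Match group"). No post-baseline variable is named.
- **Imputation.** The paragraph that opens with dichotomous outcomes ends: "Multiple multivariate imputations will be used to impute a distribution of missing values". The sentence before it speaks of primary and secondary outcomes. Neither the outcomes to be imputed nor the variables in the imputation model are given.
- **Source of the scales.** Table 1 takes HAM-D6, HAM-A6 and GAF from interview and WHO-5 from self-report, at baseline, 12 and 24 months.
- **Register data for the same people.** Table 1 lists "Labour market affiliation" and sick days from DREAM, and mental health service use from DPCR, at 12 and 24 months. The text adds that "number of days of admission, sickness absence and use of social benefits will be gathered from the DREAM database" or the DPCR.
- **Withdrawal.** Participants say which parts they leave, and the options are listed separately: "participation in the follow-up interviews, use of data collected at central registers", among others. A person can therefore stop interviews while register data stay in use.
- **Completeness.** The Discussion says: "The primary outcome is register-based, which ensures almost complete follow-up due to the comprehensiveness of Danish registers".

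**The concern.** A repeated-measures mixed model gives a valid arm contrast under missing at random when missingness depends only on what the model contains: arm, any stratification factors, and the scores already observed. Work status is not among these. Here it could matter for three reasons.

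- Work status is plausibly tied both to keeping an interview appointment and to functioning, symptoms and well-being.
- The protocol expects it to differ by arm: 45% against 30% in work or education (Power and sample size).
- Participants know their allocation (Blinding), and one arm has a mentor, most often met weekly in the first six months (Interventions). A link between work and attendance that differs by arm is therefore plausible.

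Work status is also known from the register for nearly everyone, including most of those who miss the interview. It arises after randomisation, so putting it in the effect model as a covariate would change the treatment effect being estimated. It has to enter as an auxiliary variable, through imputation or a joint model. Four of the five secondary outcomes are exposed. The fifth, days in employment or education, comes from the register.

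**Working it through.** **1. The plan's own figures.** Power for a difference d with SD s and 162 per arm, two-sided 5%, is approximately Φ(d / (s√(2/162)) − 1.96). For GAF-F the standard error is 15√(2/162) = 1.67, 5/1.67 = 3.00, and Φ(1.04) = 85.1% (Table 2: 85%). WHO-5 gives 99.7% and HAM-D6 and HAM-A6 give 99.5% (Table 2: 99% each). The plan's figures reproduce. They assume 162 observed scores per arm.

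**2. Closed form for the bias.** Let p be the proportion in work or education, and a1 and a0 the attendance of those in and not in work. The share in work among attenders is

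s = p·a1 / (p·a1 + (1 − p)·a0).

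If people in work score g points higher, the bias in the arm difference is g × [(s_IPS − s_control) − (p_IPS − p_control)].

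From the protocol: p = 0.45 and 0.30; relevant GAF-F difference 5, SD 15. Assumed, because the documents give neither: g = 10 GAF-F points, and the attendance rates below.

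| Attendance, in work / not in work | s, IPS-MA | s, control | Bias (GAF-F) |
|---|---|---|---|
| 85/60 in both arms | 0.537 | 0.378 | 10 × (0.159 − 0.15) = +0.09 |
| IPS-MA 85/85, control 85/60 | 0.450 | 0.378 | 10 × (0.072 − 0.15) = −0.78 |
| IPS-MA 90/65, control 80/80 | 0.531 | 0.300 | 10 × (0.231 − 0.15) = +0.81 |
| IPS-MA 75/85, control 85/60 | 0.419 | 0.378 | 10 × (0.0415 − 0.15) = −1.09 |

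A simulation of the same four patterns (162 per arm, baseline correlation 0.4, 800 replicates) gave +0.10, −0.75, +0.85 and −1.13 without register work status. With it as an auxiliary variable in imputation by arm, the biases were +0.05, +0.02, +0.02 and −0.06.

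The result depends on the pattern. An extreme common rule of 40/80 in both arms gives −0.36 GAF-F points. Harsher arm-specific rules give −1.07 (IPS-MA 80/80, control 80/50) and −1.76 (IPS-MA 60/80, control 80/50).

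**3. HAM-D6 with earlier scores in the model.** This is a large-sample maximum-likelihood check on baseline, 12 and 24 months. Assumed: SD 4 within work status, within-person correlation about 0.5, and people in work scoring 2 (or 4) points lower at 24 months. The relevant difference is 2 points.

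| Attendance, in work / not in work | Bias, 2-point gap | Bias, 4-point gap |
|---|---|---|
| 60/80 in both arms | 0.02 | 0.03 |
| 40/80 in both arms | 0.07 | 0.13 |
| 90/50 in both arms | −0.02 | −0.05 |
| IPS-MA 80/80, control 80/50 | 0.19 | 0.37 |
| IPS-MA 60/80, control 80/50 | 0.31 | 0.62 |

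Adding work status as an auxiliary variable brought every bias to within 0.012 of zero, which is simulation error. Earlier scores alone remove little of it.

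**4. Error rate with no true effect.** Take 30% in work in both arms and the opposite pattern (IPS-MA 75/85, control 85/60).

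- Shares in work among attenders: 0.274 and 0.378, so the bias is 10 × (−0.103) = −1.03.
- Attenders: 162 × 0.82 = 133 and 162 × 0.675 = 109.
- Standard error with baseline adjustment: 15√(1/133 + 1/109) × √(1 − 0.4²) = 1.78.
- z = 1.03/1.78 = 0.58, and Φ(−1.38) + Φ(−2.54) = about 9%.

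With a 15-point gap, z = 1.55/1.78 = 0.87 and the rate is about 14%. The simulation gave 9.4% and 15.4%, and 5.9% and 5.4% with the auxiliary variable.

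**The case against.** A reader might infer that the plan leaves the register data unused and relies on the mixed model alone for the scales. The text does not establish this. The imputation sentence follows one on primary and secondary outcomes, all five secondary outcomes are continuous, and the primary outcome is said to be almost complete, so imputation confined to it would have little to do. The imputation model's variables are not listed, and an article may leave them to the full analysis plan. This objection stands. What remains is that the article gives two approaches to missing values without saying how they fit together for the scales.

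A reader might also infer that the contrasts will be biased. The documents do not support that either: they give no non-attendance rate, no link between attendance and work, and no score gap by work status. Dependence on work is not enough by itself, because with one rule in both arms the bias is negligible. The largest figures need opposite patterns, and the 15% error rate also needs a gap of a full SD. At a 10-point gap, biases of 0.75 to 1.1 are below the complete-data standard error of 1.67. These points stand as limits on the size.

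The simulations let work status drive missingness and then condition on it, so the remedy was bound to succeed there. This is also correct; they show what is recoverable if work is the driver, not that it is. Finally, a mixed model with its assumption openly stated is standard practice. It is not an error, but this trial already collects the data to make that assumption more credible.

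**Conclusion.** The point holds as a limited improvement to a stated method. The article ties the scales to a missing-at-random model with only stratification adjustment, and leaves the reach of the imputation unclear. Register data that would make the assumption more credible are collected for the same people at the same time points.

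The possible bias is negligible if attendance depends on work in the same way in both arms. It is moderate if the link differs by arm: about 15 to 23% of the relevant GAF-F difference, and 10 to 31% of that for HAM-D6. Attendance rates, the score gap by work status and the within-person correlations are assumptions; the 45% and 30%, the SDs and the relevant differences come from the protocol. The primary outcome and days in employment or education come from the register and are not exposed to missed interviews.

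**What to change.** In the Statistical analyses section, or in the full analysis plan before unblinding, state that:

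- the planned multiple imputation covers HAM-D6, HAM-A6, GAF and WHO-5 at 12 and 24 months and is run separately by arm;
- the imputation model includes, as auxiliary variables and not as covariates in the effect model, DREAM employment or education status and days, DREAM sick days, and DPCR service use;
- the planned mixed model is fitted to the imputed data and reported beside the mixed model without auxiliaries.

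Participants who withdrew register use but left their other data in the trial contribute without the auxiliaries.

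The cost is a few sentences and a little programming; no new data or patients are needed. The limit is that the analysis still assumes missing at random given the auxiliaries, so the two sets of results should be read together.
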